### Randomization

To ensure high quality randomization and even distribution of important prognostic factors among the intervention and the control group, a web-based minimization randomization approach (Randomizer: Institute for Medical Informatics, Statistics and Documentation, Medical University of Graz, Austria; available at www.randomizer.at) is used for the 1:1 allocation of participants into the two study arms [43]. We include gender and four categories according to the initial cancer diagnosis (leukaemia and lymphoma; CNS tumours; bone tumours and soft tissue sarcomas; other diagnoses) as grouping variables in the randomization. An external collaborator who is independent of the patient recruitment and enrolment process runs the randomization and treatment allocation (Additional file 2: Table S1).

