#### Data analysis

Descriptive statistics will be used for clinical, sociodemographic and prognostic variables measured at baseline (stratified by intervention and control group). We will use frequencies and proportions with 95% confidence intervals (CI) for categorical variables and mean with ±SD or 95% CI (or median and range) for continuous variables. Descriptive analysis of baseline characteristics will be performed as soon as the baseline assessments are completed for all participants. This cross-sectional analysis will inform about the comparability of the treatment groups and the need for adjustment of between treatment group comparisons. Furthermore, baseline assessments will provide important results about characteristics, health behaviours and health status of long-term CCS in Switzerland. We will also compare the distribution of baseline sociodemographic characteristics to the Swiss Childhood Cancer Registry, to estimate the representativeness of our sample.

The primary analysis will be conducted as intention-to-treat analysis (ITT) for the primary outcome (change in composite CVD score from T0 to T12). All participants will be analysed in the group where they were originally allocated and missing data will be imputed by means of last observation carried forward (LOCF) [134]. LOCF is an appropriate procedure in this setting because it will lead to more conservative effect estimates (i.e. towards the null), because lost to follow-up is more likely to occur in the intervention group (because of an intensive and time-consuming programme) which is the group expected to change (improve). Attempt will be done to follow up all randomised participants, even if they withdraw from the allocated treatment. If the parameters of the composite CVD risk score are skewed, they will be transformed to reach normal distribution for calculating the z-scores.

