The secondary analyses include several steps: *First*, we will do the same ITT analysis with appropriate means of imputation of missing data for all the secondary outcomes. *Second*, we will perform sensitivity analysis on the primary and all secondary outcomes, including, a) complete data (complete case analysis), i.e. observations with missing information on relevant variables will be dismissed; b) analysis of intermediate effects after 3 and 6 months of intervention; c) dose-response analysis based on the actual physical activities (min of vigorous physical activities per week) or physical performance (VO_2_peak) during the period of interest, independent of the group allocation; and, d) per protocol analysis.

Per protocol analysis will include several analyses based on the actual “treatment” that the participants adhered to (independent of group allocation), first based on the reported compliance and second based on the assumed compliance. In the first analysis based on the *reported compliance*, the following participants will be analysed as being in the “intervention group”: participants randomized into the intervention group who reported in the web-diary to have reached at least 2/3 of the target physical activity (addition of 100 min of moderate to vigorous physical activities [MVPA]); and, participants who were randomized to the control group but reported in the physical activity questionnaires to have increased their physical activity level by more than 30 min of extra MVPA per week during the period of interest. The rest of the participants will be analysed as being a “control”. The second analysis of *reported compliance* will include only the participants sufficiently compliant with the protocol that they were allocated to. It will include those randomized into the intervention group who completed at least 2/3 of training volume (e.g. the addition of 100 min per week of vigorous PA) and compare them to those randomized into the control group with no more than 30 min of extra vigorous PA per week than at baseline during the period of interest.

The analysis on the *assumed compliance* will be done according to the analyses of the reported compliance but with participants being defined as compliant if they reach an increase of ≥5% in VO2peak and/or ≥10% in the ventilatory anaerobic threshold from baseline [135].

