Model selection Depending on the type of endpoint, mixed linear, logistic, Cox or Poisson regression will be used. All models will include the variables used in the adaptive randomization (age and former cancer diagnosis) and we will test the model assumptions and model fit. The models might be further adjusted for baseline values and important prognostic factors such as sex, socio-economic status, health-behaviours, treatments received, or former treating hospital if we observe an unequal distribution of important confounders between the treatment and control group.

The analysis will be done with Stata Statistical Software version 14 or newer (StataCorp LP, College Station, Texas, USA) and R Statistics (R Core Team, Vienna, Austria, www.R-project.org). A *p*-value <0.05 will be considered as statistically significant. Primary and secondary analyses will be performed when the data collection is finished for all participants.

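### The only stated trigger for adjustment beyond age and diagnosis is imbalance between the arms, which says nothing about confounding in the dose-response and as-treated analyses

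*Protocol article*

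**What the plan says.** The Model selection paragraph, under Data analysis in the protocol article, gives one adjustment rule and exempts no analysis.

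- Fixed covariates: "All models will include the variables used in the adaptive randomization (age and former cancer diagnosis").
- Condition for adding further covariates: "if we observe an unequal distribution of important confounders between the treatment and control group".
- What may be added on that condition: "The models might be further adjusted for baseline values and important prognostic factors such as sex, socio-economic status, health-behaviours, treatments received". The hospital that treated the participant is also listed.

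The opening of Data analysis shows how balance is judged. Baseline variables are described as "measured at baseline (stratified by intervention and control group"), and "This cross-sectional analysis will inform about the comparability of the treatment groups and the need for adjustment of between treatment group comparisons".

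The secondary analyses, planned as sensitivity analyses on the primary and all secondary outcomes, include two that leave the randomised comparison.

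- Item (c), dose-response: actual vigorous activity or VO2peak "during the period of interest, independent of the group allocation".
- Item (d), per protocol: analyses by the treatment "that the participants adhered to (independent of group allocation"). The first reported-compliance analysis regroups participants by the activity they reported. The second keeps only the sufficiently compliant members of each arm. The assumed-compliance analysis repeats this with fitness thresholds.

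The article gives no other confounder rule for (c) or (d).

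**The concern.** Randomisation protects the comparison of the arms as allocated. In (c) and (d) the exposure, or membership of the analysis set, is determined after randomisation by how active or fit a participant became. The confounders are then the baseline factors that predict activity and also predict the course of the outcome. The article's own optional list names plausible ones: treatments received, health behaviours, socio-economic status, sex and baseline values. Each can be evenly spread over the arms and still differ sharply between active and inactive participants.

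The Compliance section names dose-response analysis as one purpose of the compliance data, so these results will be read. If survivors with milder treatment or better health exercise more and also have better risk trajectories, that difference could be reported as an effect of exercise. The risk is greatest if (c) or (d) shows benefit where the intention-to-treat analysis does not.

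**Working it through.** **1. The texts side by side.**

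| Analysis | What defines the contrast | Does arm balance bear on confounding? |
|---|---|---|
| Primary intention-to-treat | Allocation | Yes |
| (c) dose-response | Activity or VO2peak reached | No; there are no groups |
| (d) first reported-compliance analysis | Groups relabelled by reported activity | No |
| (d) second reported-compliance analysis | Compliant subsets of each arm | No; balance of the full arms does not carry over to self-selected subsets |

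The balance check is a baseline description by arm, made once all baseline assessments are complete. Adherence of the last participants is not yet known at that point, so the check can only compare randomised arms.

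**2. The number analysed.** Under Sample size, 60 complete participants per arm and 20% loss give 60 / (1 − 0.20) = 75 per arm, which reproduces the article's figure. About 2 × 60 = 120 participants would have complete data.

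**3. Dose-response, closed form.** The inputs are assumptions: one baseline confounder with correlation r1 to dose and r2 to outcome change, no true effect of dose or arm, n = 120, two-sided 0.05. If the confounder is left out, the test statistic for dose is shifted by about δ = r1 × r2 × √120, with √120 = 10.95. The false-positive rate is Φ(−1.96 + δ) + Φ(−1.96 − δ).

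- 0.2/0.2: δ = 0.04 × 10.95 = 0.44, rate about 7%
- 0.3/0.3: δ = 0.09 × 10.95 = 0.99, rate about 17%
- 0.4/0.4: δ = 0.16 × 10.95 = 1.75, rate about 42%

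**4. Effect of the rule.** The article gives no criterion for unequal distribution, so p < 0.05 is assumed. Under randomisation the check then fires in about 5% of trials, however strong the confounding. The rate under the rule is about 0.95 × (unadjusted rate) + 0.05 × 5%:

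- 0.2/0.2: 0.95 × 7% + 0.25% = about 7%
- 0.3/0.3: 0.95 × 17% + 0.25% = about 16%
- 0.4/0.4: 0.95 × 42% + 0.25% = about 40%

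Simulation of the same setting (6,000 runs each) gives 7%, 16% and 38%. A looser trigger of p < 0.17 gives 7%, 14% and 34%. Always including the confounder gives about 5%.

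**5. As-treated, simulation.** Assumed: 150 randomised, 60% of the intervention arm and 25% of controls counted as active, no true effect, one confounder with correlation r to both uptake and outcome, 4,000 runs.

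| r | Bias, no adjustment (SD) | Bias under the rule (SD) | False positives under the rule |
|---|---|---|---|
| 0.2 | −0.06 | −0.06 | 6.4% |
| 0.3 | −0.13 | −0.12 | 12.3% |
| 0.4 | −0.23 | −0.22 | 27.7% |

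The rule removes almost none of the bias. Always adjusting brings it to about zero, with false positives of 5.0% to 5.3%. The intention-to-treat test in the same runs stays near 5%.

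**The case against.** The strongest reply concerns scope. The balance check is tied to comparisons between treatment groups, so the trigger may never have been meant for (c). The article would then simply be silent on further covariates for a sensitivity analysis, which an analysis plan not shown here may supply. Against that, the Model selection paragraph speaks of the models without exception and states a condition. A reader following it has no other instruction for (c) or (d).

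For the first analysis in (d), treatment and control group could mean the relabelled groups, where a balance check would be relevant. Likewise, a check within the compliant subsets of the second analysis could detect selection. These readings are possible, but the only check described is made by arm at baseline, and neither reading helps (c).

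Three stronger inferences are tempting and not supported:

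- A reader might conclude that (c) and (d) run wholly unadjusted. They do not: age and diagnosis are always in, and diagnosis partly stands in for treatment received.
- A reader might conclude that the rule forbids adjustment when the arms are balanced. The wording is permissive, so it neither requires nor forbids it. That leaves the choice open, with a stated condition that is uninformative here.
- A reader might conclude that the trial's main result is at risk. The primary comparison is by allocation and is untouched.

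The objection to the size also stands in part. The correlations are invented, age and diagnosis are not modelled as already removing part of the confounding, and at 0.2/0.2 the excess over 5% is small.

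**Conclusion.** The point holds for the sensitivity analyses only. The one stated trigger for adjustment beyond age and diagnosis cannot detect confounding in the dose-response analysis. On the reading that the article's own balance check supports, it cannot detect it in the per-protocol analyses either. In the usual case of balanced arms, these would be adjusted for no more than age and diagnosis.

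The illustrative cost is a false-positive rate of 7% at 0.2/0.2 and 16% at 0.3/0.3 for dose-response, against 5%. The figure near 40% needs a single baseline factor correlated 0.4 with both dose and outcome change, over and above age and diagnosis, and should not be taken as expected. All sizes assume one measured confounder and an assumed significance trigger. The return to 5% with adjustment is a property of that setting; in the trial, unmeasured factors such as motivation would remain.

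This is worth correcting before analysis. It does not threaten the primary conclusion.

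**What to change.** In the Model selection paragraph:

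1. Limit the imbalance sentence to the comparisons of the randomised arms, if it is kept.
2. State that the models for items (c) and (d) always include a pre-specified set, irrespective of arm balance: baseline value of the outcome, age, sex, diagnosis group, socio-economic status, baseline health behaviours and treatments received. Say whether former treating hospital, also on the article's list, belongs to the set.
3. State that these analyses are reported as observational, with residual confounding acknowledged.

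Naming sex in the set also deals with a related slip. The Randomization section says "We include gender and four categories according to the initial cancer diagnosis", whereas Model selection gives age and diagnosis as the randomisation variables and leaves sex on the optional list. The two passages should be reconciled.

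The cost is one or two sentences and a few degrees of freedom in secondary analyses of about 120 participants. No new data are needed: Personal history and clinical examination covers cancer history, the medical record, socio-demographic characteristics and health behaviours at baseline.

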#### Publication policy

Because of the large variety of outcomes assessed, we intend to publish the effect of the intervention on the different outcomes in more than one paper. We intend to publish the effect of the intervention on our primary outcome (CVD risk score) and related single cardiovascular disease risk factors, glycaemic control and body composition in a single paper (main paper). This publication will also include the changes in physical fitness and physical activity as well as the clinical status and safety endpoints. Beside this, we intend to publish the effect of the intervention in different papers of the following topics:

- Effect on bone health

- Effect on quality of life, mental health and well being

Results of the baseline assessments only and further in depth research questions will be published in additional papers of meaningful topics.

## Discussion

It’s estimated that 1 in 800 young adults under the age of 35 years living in developed countries is a survivor of paediatric cancer [2]. Unfortunately, studies have shown that the vast majority of these survivors present with chronic medical conditions such as cardiovascular and pulmonary diseases, 2nd cancers, overweight, osteoporosis, or psychological distress, directly impacting their late mortality, morbidity and quality of life [4, 7, 117, 136].

Physical activity and exercise have become a cornerstone in the prevention and treatment of chronic diseases including cancer, cardiovascular morbidity and mortality, diabetes, osteoporosis, fatigue or increasing psychological well-being [11, 16, 137–147] Even in palliative care, physical activity seems to reduce the burden of cancer- or therapy-related side effects [148]. Despite these striking evidences, there is a lack of randomized, controlled exercise trials aiming to reduce cancer- and therapy-related sequelae in paediatric cancer survivors, which may ultimately increase life expectancy, decrease morbidity and lead to an improvement in quality of life. This is especially important for childhood cancer survivors as these patients are young with a long life in front of them.

Besides contributing to the body of scientific knowledge, this randomized controlled trial will also use a novel approach with a personalized and partially supervised exercise intervention. The intervention is supported by multiple tools such as web-based feedback, pedometers and individually tailored counselling. With this approach, we try to overcome barriers and low compliance that is a major problem in the sustainability of intervention studies. Moreover, the measurement of most major cardio-metabolic risk factors and bone health and the inclusion of patient important outcomes like quality of life and psychological distress provide a complete picture.

Another new aspect is the precise measurement of bone architecture including a broad battery of possible determinants of osteoporosis or decreased bone mass in CCS. This may shed more light on the single and combined risk factors of increased bone fracture risk or osteoporosis in this population and on the potential preventive approaches.

The planned physical activity intervention has the potential to become an important pillar in the support of the whole CCS population. The project will evaluate whether a 1-year partially supervised program including exercise counselling with motivational feedback in CCS (aged 16 years and above) is able to reduce long-term sequelae and/or lifestyle-related diseases including but not limited to cardiovascular and metabolic risks as well as bone health, physical fitness, mental health, and quality of life. If the program shall prove effective, the SURfit material will become available to interested national and international clinics that treat and/or follow-up childhood cancer patients to promote exercise in their CCS.

## Abbreviations

ASHT: American Society of Hand Therapists
BAP: Bone-specific Alkaline Phosphatase
BMC: Bone Mineral Content
BMD: Bone Mineral Density
BSI: Brief Symptom Inventory
CCS: Childhood Cancer Survivor
CDC: Centre of Disease Control and Prevention
CI: Confidence Interval
CIS: Checklist Individual Strength
CNS: Central Nervous System
cOC: Carboxylated Osteocalcin
CSA: Cross-sectional Area
CTCAE: Common Terminology Criteria for Adverse Events
CTX: C-terminal Telopeptide of Type I Collagen
CV: Coefficient of Variation
CVD: Cardiovascular Disease
DXA: Dual X-Ray Absorptiometry
E2: Estradiol
ECG: Electrocardiogram
EFP: European Forearm Phantom
EIA: Enzyme-Immunoassay
EKNZ: Ehtikkommision Nordwest und Zentralschweiz
EMI-2: Exercise Motivations Inventory
FSH: Follicle-stimulating Hormone
fT4: free Thyroxine
GSI: Global Severity Index
HA: Hydroxyapatite
HbA1c: Glycated Haemoglobin
HDL: High Density Lipoprotein Cholesterol
HOMA-IR: Homeostasis Model Assessment – Insulin Resistance
ICCC-3: International Classification of Childhood Cancer – 3rd Edition
IGF-1: Insulin Like Growth Factor 1
IGF-BP3: Insulin Like Growth Factor Binding Protein 3
iPTH: Intact Parathyroid Hormone
IR: Insulin Resistance
ITT: Intention to Treat Analysis
LDL: Low Density Lipoprotein Cholesterol
LH: Luteinizing Hormone
LOCF: Last Observation Carried Forward
LRC: Lipid Research Clinics questionnaire
MCS: Mental Component Summary
OC: Osteocalcin
oGTT: oral Glucose Tolerance Test
PA: Physical Activity
PAR: Seven-Day Physical Activity Recall Questionnaire
PCS: Physical Component Summary
PINP: N-terminal Propeptide of Type I Procollagen
p-QCT: Peripheral Quantitative Computed Tomography
RCT: Randomized Controlled Trial
RPE: Rating of Perceived Exertion
SD: Standard Deviation
SF: Skinfold
SF-36: Short Form-36
SOP: Standard Operational Procedure
SPOG: Swiss Paediatric Oncology Group
STS: 1-min sit-to-stand
SURfit: Survivor Fitness Study
T0, T3, T6, T12: Time point 0, Time point 4 months, Time point 6 months, Time point 12 months
TBS: Trabecular Bone Score
TSH: Thyroid-stimulating Hormone
TT: Total Testosterone
ucOC: Uncarboxylated Osteocalcin
UKBB: University Children’s Hospital Basel
VAS: Visual Analogue Scale
VFA: Vertebral Fracture Assessment
VO_2_peak: Peak Oxygen Uptake
Wpeak: Peak Performance in Watt
